### 6.4.3 Materials

The BCI contains two broad categories of components:

- i. CFHealthHub behaviour change modules including adherence feedback used by PWCF and health professionals
- ii. The behaviour change manual and toolkit used by the interventionist in interactions with PWCF in order to understand the specific barriers to adherence for that individual, and to tailor and personalise delivery of the behaviour change modules accordingly.

### 6.4.4 Procedures

The BCI will be delivered over a 4 to 6 month period through a combination of face-to-face sessions and contact via telephone with an interventionist, and through participant interaction with different modules of content available on CFHealthHub. The interventionist will discuss participant data with members of the MDT to ensure that care is informed by objective adherence data. If any concerns become apparent as the interventionists collect data and work with participants, these concerns will be passed onto the clinical team. The clinical team will

follow their standard procedures in relation to any concerns raised. The intervention content and delivery flow are outlined in Figure 5 and described below:

#### *6.4.4.1 Consent Visit (all participants)*

At the consent visit participants will be given a chipped nebuliser (eTrack) and Qualcom hub or the participants will receive a visit from a clinical trainer who will convert the participant's I-neb to a Bi-neb by adding a Bluetooth chip and providing a Smartphone hub. The clinical trainer may set up the Bi-neb in the patient's home or at hospital either during the main consent visit or at a separate visit after consent has been obtained. Both the eTrack and Bi-neb will connect to CFHealthHub which will enable adherence data be collected. The interventionist will input the participant's prescription details into CFHealthHub. Together these will allow the system to generate adherence charts for that participant. At this visit participants will complete a range of baseline measures (see Table 3) including the COM beliefs and barriers questionnaire (COM-BMQ) which will be entered into CFHealthHub. The responses to this questionnaire will be used to populate the 'My toolkit' section of CFHealthHub with specific tailored elements from the 'My treatment' modules prior to the Initial Intervention Visit. The participant's pseudomonas status will be clarified at baseline and confirmed by the PI with the opportunity to compare the participant's prescription with the pseudomonas status.

#### *6.4.4.2 Initial Intervention Visit (intervention arm only)*

Participants will be introduced to CFHealthHub. They will be asked to complete an online consent form on behalf of their NHS trust in which they will specify what additional data they would be willing for CFHealthHub to record and display (e.g. name, and uploaded photographs) and what functional options they would like access to (e.g. push notifications). Permissions may be changed at any time. The participant will have the option to upload their own "patient story" into CFHealthHub after completion of the online consent form.

The interventionist will discuss their motivation to adhere to their nebuliser treatment, will address beliefs associated with poor adherence and will refer back to answers on the COM-BMQ to elicit the participants beliefs associated with adherence. Participants will be shown 'My toolkit' which will have been prepopulated with tailored motivational content (see consent visit).

The interventionist and participant will look at and discuss the adherence charts on CFHealthHub with a focus on period of higher adherence. The interventionist will note any barriers raised by participants during this discussion.

The interventionist will support the participant to identify where and when additional nebuliser treatments could be fitted into their schedule and support them to make an action plan using the online tool available on CFHealthHub. This action plan will be saved to the 'My toolkit' zone. The interventionist will then agree a % adherence goal for the next four to six weeks based on the number of additional treatments that have been planned. This will be recorded on CFHealthHub and will be represented by a target line on the adherence charts.

If motivation is so low that participants are reluctant to set an action plan/goal then the interventionist will spend further time discussing motivation and will skip to confidence building (see below).

The interventionist will encourage participants to focus on likely problems or issues that might disrupt the achievement of the adherence goal and will use the Problem-solving module on CFHealthHub to address each of these anticipated problems. The Problem-solving module includes solutions based on educational content, practical support (e.g. model letters to

employers) and interactive tools. Relevant solutions will be saved to the 'My Toolkit' zone of CFHealthHub.

The interventionist will discuss the participant's confidence to meet their goal and will identify 2-3 'talking heads' videos showing other people with CF addressing and overcoming similar barriers to nebuliser adherence.

The visit will conclude with a review of the goal and the tailored and personalised contents saved to the 'My toolkit' zone of CFHealthHub. The interventionist will encourage a learning mindset, emphasising that even if adherence doesn't increase starting to think about adherence will produce learning that will make subsequent attempts to change easier.

#### *6.4.4.3 Participant Independent access to CFHealthHub (intervention arm)*

Participants will have independent access to CFHealthHub at all times following the Baseline visit. They can, at any time, access their adherence charts, 'My toolkit' contents, and can browse the other areas of content as they wish. Frequency of access to each area of CFHealthHub will be monitored and recorded.

Adherence charts will provide colour -coded feedback about participant achievement towards their adherence goal so that they are provided with immediate, easy to recognise information about their achievements. Subject to consent, participants will be sent encouraging messages via push notifications, or alternatively when they access CFHealthHub, to match the progress made e.g. congratulations on achieving their goal, congratulations on having made progress towards their goal, encouragement to remember their action plan.

#### *6.4.4.4 Review visit (Visit 3 - intervention arm)*

At the review visit, the interventionist and participant will look at and discuss the adherence charts on CFHealthHub and goal achievement with a focus on progress made and periods of higher adherence.

If the adherence goal was met then the participant will be encouraged to set a new higher adherence goal or to a goal to maintain their current level of adherence which will be recorded on CFHealthHub. Following this the participant and interventionist will review the contents of 'My toolkit' and revise action plans, problems/solutions as required. If issues of motivation are still a concern the interventionist may recommend additional/alternate elements of content from 'My treatment' or 'Talking heads' to go into 'My toolkit'.

If the adherence goal was not met then the interventionist and participants will discuss the barriers to goal achievement (motivation, capability, opportunity). The interventionist will address beliefs associated with poor adherence and will add/revise the elements of content from 'My treatment' or 'Confidence building' to go into 'My toolkit'.

If no goal was previously set then the interventionist will review motivation and confidence and then will consider if the participant is ready to action plan and set a goal. If not they will spend more time reviewing motivation and confidence.

The participant will be encouraged to set a realistic % adherence goal for the next four to six weeks and this will be recorded on CFHealthHub. The interventionist will support the participant to revise their action plan as needed and save this to the 'My toolkit' zone. Based on the earlier discussion about the barriers that prevented goal achievement the Problem-solving module on CFHealthHub will be used to address each of the problems encountered, and any that are anticipated. Relevant solutions will be saved to the 'My Toolkit' zone of CFHealthHub.

The visit will conclude with a review of the goal and the tailored and personalised contents saved to the 'My toolkit' zone of CFHealthHub. The interventionist will re-emphasise a

learning mindset, emphasising that the participant cannot fail, but can learn from the process so that they can work together on the adherence challenge.

Participating centres will provide participants with contact details, typically telephone numbers, but other methods may be volunteered by centres. Contact details will be provided so that participants can contact the centre if they have queries or problems regarding CFHealthHub between visits. The interventionist will be able to feedback any information from the intervention delivery **after** the baseline intervention visit to members of the wider CF team. This may include adherence data from sessions with the participant's clinician and MDT particularly if the participant raises any concerns or issues e.g. side effects of a drug to allow their usual clinician to discuss this with them at their next clinic visit.

#### *6.4.4.5 Subsequent Review (intervention arm)*

Following these two sessions the amount of interaction which each PWCF has with the interventionist will be tailored to their needs and requirements although it is anticipated that these will normally marry with routine clinic visits: They may have additional face-to-face sessions or contact via telephone or e-mail. No more than one monthly face-to-face session will be conducted because of the research protocol; if the participant requests additional support, the centre may accommodate this at their discretion. Review meetings will take 30 minutes and be conducted over the 5month (+/- 1 month) of the follow-up period. The structure of review sessions will follow the same pattern as for 6.4.4.4.

#### *6.4.4.6 Final research visit (5 months +/- 1 month from consent)*

All participants will complete a final research visit 4-6 months from the date of consent. At this visit the interventionist will collect the primary and secondary outcome data (see table 3) including demography data, health care resource use and the participant completed questionnaires. At this final research visit the interventionist will re-check that all adherence data has been transferred to CFHealthHub. The eTrack can store approximately 6 months of treatment data, ensuring all the data is transferred at this visit should help to prevent missing data.

Following the final 4-6 month post-consent research visit, we will continue to collect: adherence data from CFHealthHub; exacerbations; FEV1 and ask participants the subjective adherence question until, 30th April 2017. At this point the study closes and the involvement of all participants ceases. After the trial ends (30/4/17), the aspiration is to allow participants in the control to have access to the intervention for which negotiations are ongoing. Currently funding is in place for the trial interventionists at study sites to deliver the intervention only over a 12-month period i.e. up to 30/4/17. It is anticipated that CFHealthHub used outside the trial would be delivered within the existing resources of the MDT so using CFHealthHub outside the trial should not need the trust to employ any additional staff members. As this is a pilot feasibility study where we are testing the intervention in participants, there is an expectation that further iteration of CFHealthHub may occur.

Figure 5. Behaviour change intervention flow chart

[figure not shown]

## 6.5 Usual care

Patients in both arms will receive usual care. Usual care is heterogeneous within and between centres, based on the needs of patients and the skills and interests of CF Unit staff. To better understand the configuration of usual care at participating centres a survey tool will be administered by the CTRU to the lead clinician at the centre. This will identify the spectrum of clinical and behaviour change interventions that are in use in the management and self-management of CF.

A minor component of the intervention is to train all members of the MDT in awareness of patient activation so that they are open to addressing issues raised for PWCF in the intervention arm. In addition, a staff member in the MDT will help to deliver the intervention. There is the possibility that the awareness of patient activation will have some effect on PWCF in both the intervention and control arms, and of leakage of the learning from the behaviour change component of the intervention to controls. We will investigate this possibility during the process evaluation.

Members of the MDT at each centre will receive one half-day, on-site, face-to-face training about the importance of objective nebuliser adherence data in the management of CF, and awareness of the importance of building patients' knowledge, skills and confidence to enable them to self-manage their treatment. This will include training in the interpretation of graphs and charts of objective adherence data produced by CFHealthHub, and the rationale for reducing target adherence in poor adherers in order to increase confidence. This will be delivered by designated members of the ACtiF research team.

Participants in the control arm will use a microchipped nebulizer but will not be able to access adherence data or other content and tools through CFHealthHub, neither will they receive the structured CFHealthHub intervention as described in the intervention manual. Control arm participants using Bi-neb nebulizers might have access to their data as part of routine care but this will not be in the user friendly format provided by the intervention.

One function of the qualitative research interviews with staff and control participants (see Section 8 below) is to understand the extent to which the patient activation awareness training has affected staff behaviour and whether control arm participants have received some aspects of the behaviour change intervention.

## 6.6 Criteria for discontinuing or modifying allocated interventions

There are no criteria for discontinuing treatment. Participants will be made aware that their participation is voluntary and they may discontinue study interventions, should they wish, at any time.

If a participant wishes to withdraw from treatment they will be able to speak to a member of the site study team i.e. ACtiF interventionist. This will be documented on a participant withdrawal form, within the Case Report Form. Any data already collected during the course of the trial up to the point of withdrawal will be used in the final analysis. We will ask the participants for their permission to continue to collect the primary outcome data i.e. CF exacerbations. The participant or clinician can make the decision to discontinue the allocated study intervention for any reason.

Participants will have the following options if they wish to withdraw:

1. Withdraw from the intervention i.e. intervention delivery visits only but will remain in the study. Patients can continue to use CFHealthHub. All study data would continue to be collected at subsequent follow up time points as per protocol.
2. Withdrawal from the study. Unless the patient objects, any data collected up to this point would be retained and used in the study analysis. The local interventionist would ask the participant if they agree to the collection of primary outcome data as defined in the protocol and or adherence data If

they agree to collection of adherence data, CTRU and or interventionist will continue to follow up participants for adherence data.

3. Withdrawal from the trial entirely. Unless the patient objects, any data collected up to this point would be retained and used in the study analysis. If the patient does not wish to be contacted with regard to primary outcome data or adherence data, no further contact with regard to the study will be made. If the participant does specifically request for all their data to be removed information regarding the participant will be retained at site, as part of the patient notes, along with their withdrawal form and request to delete the data.

A participant would be classed as complete if they have continued in the study until the last protocol defined visit, however there may be missing visits and / or data.

### ***Loss to Follow-Up***

A participant would be classed as lost to follow up if the participant has 1) not completed the study or 2) been withdrawn despite attempts for further contact, as per protocol, having been made. Unless the participant withdraws from the study entirely we will continue to collect the primary outcome data when possible (i.e. from medical notes).

This withdrawal section has been developed in accordance with the CTRU Participant Discontinuation and Withdrawal of Consent Standard Operating Procedure (SSU003).

## **6.7 Strategies to improve adherence to intervention protocols**

### **6.7.1 For health professionals**

The intervention protocols will be described in detail in an intervention manual. Interventionists will be trained to deliver the intervention according to the manual protocols. Interventionist training (as a form of behaviour change) will focus on Capability, Opportunity and Motivation. It will utilise evidence about the importance and likely effectiveness of the intervention and will challenge common misconceptions about adherence. Skills training and an introduction to the tools available on CFHealthHub will increase staff capability, and we will work with clinics and clinicians to ensure that the practical requirements for intervention delivery are in place: space, time etc (opportunity).

CFHealthHub will record interventionist access to the site. It will also automatize some of the tailoring of the intervention according to the COM-BMQ which will be completed online. The contents of 'My Toolkit' will be recorded for each participant so that we will have records of what content they have been recommended. Interventionists will also be required to complete session records each time that they deliver the intervention to record the decisions made and the reasons for these,

### **6.7.2 For patients**

Where participants provide consent we will send optional push notifications to encourage engagement with CFHealthHub. For example, we will send congratulatory messages when adherence improves, encouraging messages to remind participants to engage with the content. Face-to-face visits will, where possible be arranged to coincide with clinic visits as per usual care, therefore minimising the additional burden on participants.

## **6.8 Relevant permitted / prohibited concomitant care**

No concomitant care will be denied based on the research protocol.

## 7. Outcomes

### 7.1 Feasibility outcomes ('stop-go' or 'success' criteria for RCT)

In line with proposed CONSORT extension for pilot studies [37], in this section, we state the criteria for success of the external pilot trial. The criteria are based on the primary feasibility objectives, which provide the basis for interpreting the results of the external pilot and for determining the feasibility of proceeding to the full-scale study scheduled for months 31 to 60 of the project. Depending on the funder's perspectives, the outcome of the external pilot might be:

- (i) "Stop - main study not feasible";
- (ii) "Continue, but modify protocol - feasible with modifications";
- (iii) "Continue without modifications, but monitor closely - feasible with close monitoring"; or,
- (iv) "Continue without modifications - feasible as is." [37]

We anticipate that modifications to the research protocol will be necessary as the feasibility study progresses. Some of the qualitative research will be undertaken early in the pilot trial and lessons learned about the trial procedures will be identified and acted on during the pilot trial. There are three objective stop-go criteria:

#### **1. Feasibility of recruitment to RCT**

Defined as recruitment of no fewer than 48 participants randomised at two centres over four months, 75% of the rate required in the main trial;

#### **2. Feasibility of retaining participants in the RCT**

Defined as attrition from the research protocol of no more than 15% of randomised participants at 5 (+/-1) months.

If these are met the full trial will go ahead. If these are not met overall, but are met in the last half of the pilot trial after trial procedures have been improved based on lessons learned from the early stage of the pilot trial, then the full trial will go ahead.

### 7.2 Process data relating to the implementation of the trial

#### **1. Number and characteristics of eligible patients approached for the study**

Collected by centres in screening logs and transferred to Prospect database

#### **2. Reasons for refused consent**

Collected by centres in screening logs and transferred to Prospect database.

#### **3. Reach**

How many participants are consented into the study, sub-grouped by socio-economic status (from CF Registry), as a proportion of:

- Those approached, expressed quantitatively, based on 'pre-screening' logs completed by ACTiF interventionist;
- Those known to be eligible, expressed quantitatively based on CF Registry.

#### **4. Participant attrition rate**

Collected by centres in screening logs and transferred to Prospect database.

### **5. Reasons for attrition**

Collected by centres in screening logs and transferred to Prospect database.

### **6. Maintenance:**

The processes by which participants are kept involved in the collection of key secondary outcome data research data:

- The extent to which adherence data is successfully uploaded from the chipped nebulisers , described quantitatively using CFHealthHub (Intervention arm only).

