### **7. Number of missing values/incomplete cases**

Assessed by data management team, based on data in Prospect database.

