| MAD-3 (Medication Adherence Data-3 items)                                                                                                                                                                                                                                                                                                                                                                     | Prospect | PWCF          | ●             | -                             | -                | -                     | ●                                         | -                                 |
| COM-BMQ                                                                                                                                                                                                                                                                                                                                                                                                       | Prospect | PWCF          | ●             | -                             | -                | -                     | ●                                         | -                                 |
| Objective adherence                                                                                                                                                                                                                                                                                                                                                                                           | CFHH     | CFHH          | ●             | -                             | ●                | -                     | ●                                         | -                                 |
| Subjective adherence single question                                                                                                                                                                                                                                                                                                                                                                          | Prospect | PWCF          | ●             | -                             | ●                | -                     | ●                                         | ●                                 |

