| Duration of inhalation                                                                          | Nebuliser              | ●                             | ●                                            | -                | -                | -                                         | x                       |
| Accessing CFHealthHub – look at adherence data                                                  | PWCF                   | ●                             | ●                                            | -                | -                | -                                         | x                       |
| Accessing CFHealthHub – look at ‘My Toolkit’                                                    | PWCF                   | ●                             | ●                                            | -                | -                | -                                         | x                       |
| Accessing CFHealthHub problem solving / education / talking heads pages outside of ‘My Toolkit’ | PWCF                   | ●                             | ●                                            | -                | -                | -                                         | x                       |
| Accessing CF HealthHub – first to last click in a session                                       | PWCF                   | ●                             | ●                                            | -                | -                | -                                         | x                       |

\*Adherence data collected for both research and control arms

+ Monthly prescription checked by CTRU centrally to alert local interventionists to any potential changes in control arm and potentially also intervention arm

X data continued to be collected in CFHealthHub and interventionist responds for those participants who have “opted in” to receive intervention till 30/4/17

To be broken down in statistical analysis plan.

**Figure 6. Participant timeline for the external pilot RCT**[figure not shown]

\*When I-nebs are converted to Bi-nebs a representative from the company (Philips) will do this between the consent visit and first intervention visit.

The study recognises that flexibility in accommodating participant schedules may cause time windows to change but this will allow us to adapt the intervention for the main RCT.

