#### ***Plans to promote participant retention and complete follow-up.***

Participant retention will be ensured by the following procedure:

1. At each point of contact, the interventionist will check with the participant that the Qualcomm hub or Smartphone hub is plugged in and turned on. A member of CTRU who is performing data and prescription checks may alert the interventionist. They will remind the participant of the proximity required for data transfer (10 metres)
2. In the event of no data being displayed in CFHealthHub for a period of at least a week (and the participant is not known to be on holiday) the interventionist will make contact with the participant (Email/Text/Telephone call) to check that the following
  - That the Qualcomm or Smartphone hub is plugged in
  - That the Qualcomm hub is working (showing solid green and yellow lights on the display)
  - That they have been within range of the Qualcomm hub sufficient to facilitate data transfer (10 metres)
  - That the Smartphone hub is switched on (showing the locked 'password' screen when any button is pressed)
  - That the Bi-neb and Smartphone hub have been kept in the same room, or at least have been in close proximity at some point during the day.

Any participants using the Bi-neb who are still experiencing issues after following the steps above, may receive a face to face or telephone support (at home or hospital) from the clinical trainer to resolve any outstanding issues.

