#### ***Troubleshooting:***

Data capture will be monitored both by interventionist at the site and centrally by the CTRU. In the event of data not being uploaded patients will be contacted to trouble shoot problems. Patients will be offered support to suit their circumstances including home visits (conducted by the members of the site research team) where necessary.

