## 11. Data analysis

### 11.1 Quantitative analysis

The analysis will be performed after data lock by a CTRU statistician under the supervision of the senior study statistician. As the trial is a pragmatic parallel group RCT data will be reported and presented according to the CONSORT 2010 statement [61] with reference to proposed extension for pilot / feasibility studies [37]. As a pilot/feasibility study the main analysis will be mainly descriptive and focus on confidence interval estimation and not formal hypothesis testing [58]. We will report rates of consent, recruitment and follow-up by centre and by randomized group.

Clinical outcome measures will be summarised overall and by randomized group. Baseline demographic (age, gender), physical measurements (e.g. weight, height, BMI), and patient reported outcome measures (EQ-5D, PAM-13, Assessment of Routine, MAD-3, SRBAI, CFQ-R, GAD-7, COM-BMQ, PHQ-8), and clinical measurements (e.g. FEV1, IV days in last registry year ) will be described and summarised overall and for both treatment groups.

The primary outcome is the number of pulmonary exacerbations treated with IV antibiotics over the 6 month post-randomisation follow-up period. We will also include, as part of the feasibility analysis, estimation of the effect size for the 6-month pulmonary exacerbations outcome with 95% confidence interval estimates to check that the likely effect is within a clinically relevant range (as confirmation that it is worth progressing with the full trial). For this we will use a Poisson generalised linear model (GLM). Secondary continuous outcomes such as six-month post randomisation FEV1, BMI EQ-5D, PAM-13, Assessment of Routine, MAD-3, SRBAI, CFQ-R, GAD-7, COM-BMQ, PHQ-8) will be analysed with a multiple linear regression model with the baseline value of the outcome and randomised group as covariates. The treatment group coefficient and its associated 95% confidence interval will be reported from the various multiple linear regression models. The mean level of adherence (to prescribed medication) between the intervention and control groups over the 6 month post-randomisation follow-up period will also be reported and compared between the groups and a 95% confidence interval (CI) for the mean difference in this parameter between the randomised groups will also be calculated.

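### The protocol plans to describe nebuliser upload completeness in the intervention arm only, although objective adherence is compared between both arms

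*Protocol*

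**What the plan says.** Section 7.2 lists process data on how the trial is implemented. Item 6 (Maintenance) covers how far adherence data are successfully uploaded from the chipped nebulisers, "described quantitatively using CFHealthHub (Intervention arm only"). The restriction is written into the protocol; it is not a detail left open.

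Elsewhere adherence is a two-arm outcome:
- Section 6.5: "Participants in the control arm will use a microchipped nebulizer". Section 6.4.4.1 has both device types connecting to CFHealthHub for all participants.
- Table 4 is titled as covering the research arm, but its footnote states: "Adherence data collected for both research and control arms".
- Section 11.1 compares mean adherence between the groups, and "a 95% confidence interval (CI) for the mean difference in this parameter between the randomised groups will also be calculated".

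The neighbouring measure, section 7.2 item 7 on missing values, is "Assessed by data management team, based on data in Prospect database". In Table 3 the row "Objective adherence" gives CFHealthHub, not Prospect, as its location.

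On day-to-day running, section 10.1.1 says: "Data capture will be monitored both by interventionist at the site and centrally by the CTRU". It also says: "At each point of contact, the interventionist will check with the participant that the Qualcomm hub or Smartphone hub is plugged in".

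**The concern.** An outcome is to be compared between two arms, yet its completeness is to be described in only one of them. A reader of the pilot results would see how well device data arrived from participants receiving the intervention, with no planned counterpart for controls.

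The protocol gives reasons why upload might differ by arm. The hub is checked at each contact with the interventionist, and the intervention arm has an initial visit, a review visit and further tailored contacts (sections 6.4.4.2, 6.4.4.4 and 6.4.4.5). Intervention participants can look at their charts in CFHealthHub at any time (section 6.4.4.3). Controls cannot, although section 6.5 allows that Bi-neb users may see their data in another form through routine care.

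Two things are at stake. One is how far the between-arm adherence estimate can be interpreted. The other is what the pilot is for: objective 2(b) in section 3.2 is to understand and mitigate potential sources of failure in the full trial. Whether participants who get no feedback from CFHealthHub go on transmitting data for months is a question of that kind.

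**Working it through.** No stated figure is in dispute, so the main check sets the relevant passages side by side.

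1. **Does the control arm generate upload data?** Yes (sections 6.4.4.1 and 6.5; Table 4 footnote).
2. **Is the outcome compared between arms?** Yes, with a 95% confidence interval (section 11.1).
3. **Does the upload measure cover both arms?** No (section 7.2, item 6).
4. **Does another planned measure clearly fill the gap?**
   - Item 7 counts missing values in Prospect, while Table 3 places objective adherence in CFHealthHub.
   - The monthly review of missing-data rates in section 10.1.3 sits within the description of Prospect.
   - The follow-up rates by group in section 11.1 show who remained in the study, not whether their device data arrived.
5. **Is capture watched operationally in controls?** Yes. None of the following is limited to one arm: monitoring by site and CTRU, monthly CTRU calls, contact after at least a week without data (all section 10.1.1), and the transfer re-check at the final visit (section 6.4.4.6). These are troubleshooting steps, however, not a reported measure by arm.

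**Illustration of what a difference in upload could do.** The only input from the protocol is adherence of 36% (section 2.1, a median from a cited study), used here as the true level in both arms. The upload rates are assumed, and so is the rule that doses not uploaded count as not taken. Then

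spurious difference = true adherence × (upload in intervention arm − upload in control arm).

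| Upload, intervention | Upload, control | Calculation | Spurious difference |
|---|---|---|---|
| 95% | 95% | 0.36 × 0.00 | 0.0 points |
| 95% | 90% | 0.36 × 0.05 | 1.8 points |
| 95% | 80% | 0.36 × 0.15 | 5.4 points |
| 90% | 95% | 0.36 × (−0.05) | −1.8 points |

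The last row is there because the sign is not known. The formula also assumes that the data are lost for good. Section 6.4.4.6 says the eTrack stores about six months of treatment data, so transfer at the final visit would recover much of any shortfall on that device. No storage figure is given for the Bi-neb.

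**What a table by arm could show.** With the target of 64 participants allocated equally, there are 32 per arm. Treat upload, for simplicity, as one yes/no result per participant. The 95% half-width for the difference between arms is 1.96 × √[p₁(1 − p₁)/32 + p₂(1 − p₂)/32]:
- 95% against 90%: 1.96 × √(0.0475/32 + 0.09/32) = 0.128, about 13 points.
- 95% against 80%: 1.96 × √(0.0475/32 + 0.16/32) = 0.158, about 16 points.

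The table would be descriptive. It could reveal a large imbalance but could not rule out a modest one.

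**The case against.** The strongest reply is that control-arm upload is already looked after. Control data reach CFHealthHub, several capture checks apply to everyone, and all participants have a final visit at which transfer is re-checked. Central prescription checks, which also serve to check data transfer (section 7.4.2, item 16), are described under Table 4 as alerting sites to changes in the control arm and potentially also in the intervention arm. This stands. A reader might infer from item 6 that differential loss cannot be detected; the documents do not support that, because it could be tabulated from data the trial holds.

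A reader might also infer that controls will lose more data and that the comparison will therefore favour the intervention. The protocol shows a plausible mechanism, but it also describes safeguards that may offset it. Neither the size nor the direction of any difference is established.

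It can also be said that section 10.1.1 names CFHealthHub among the sources whose data are entered on the CRF or Prospect, so the missing-values count might include adherence. That wording leaves some ambiguity, but Table 3 names CFHealthHub for this item, so the coverage is at best unclear.

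Finally, the protocol does not say how days without upload are counted. Section 7.4.3 refers further outcome detail to the statistical analysis plan, so no fault can be found on that point here. Adherence is also a secondary outcome in a mainly descriptive pilot and enters no stop-go criterion, which limits the consequence.

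**Conclusion.** The point holds in a limited form. The protocol restricts its planned description of upload completeness to the intervention arm while comparing adherence between arms, and no other planned measure clearly covers the controls. This makes the pilot less informative about an outcome the full trial would also need to obtain from controls. It does not show that the adherence comparison is biased.

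The 1.8 and 5.4 points are hypothetical. They rest on assumed upload rates, on permanent loss, and on a zero-counting rule that the protocol does not state. The finding itself needs none of these assumptions; it follows from the text. The change is worth making because the restriction is explicit, the data already exist and the correction costs little.

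**What to change.** In section 7.2, item 6, delete the parenthesis that limits the measure to the intervention arm. Apply whatever definition of successful upload is used for that arm to both arms, and report it by randomised arm and by device (eTrack, Bi-neb) next to the between-arm adherence comparison in section 11.1.

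The source is data already held in CFHealthHub, so no new collection is required. The cost is a wording change and one extra table. Sample size and power are unaffected. How days without upload enter the adherence calculation belongs in the statistical analysis plan and is not part of this change.
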